## Protocol

### Design and setting

A double-blind, placebo-controlled randomized (1:1) Phase 2 trial evaluating the efficacy, safety and tolerability of adjunct metformin versus placebo for 24 weeks, in addition to standard-of-care MDT (rifampicin 600mg and clofazimine 300mg once a month supervised, 50mg of clofazimine and 100mg of dapsone daily unsupervised) in the management of individuals with newly diagnosed MB leprosy (
Figure 1). The study will take place in five primary health centers (puskesmas) in Jayapura, Papua, and Gowa, Sulawesi, which are areas of high endemicity of leprosy in Indonesia, most of which are MB leprosy. This is protocol version 5.0, dated January 30
^th^ 2024.

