### Outcomes

**
*Primary efficacy outcome*
**

The proportion of participants experiencing a LR during study follow-up (total 48 weeks).

**
*Primary safety outcome*
**

The proportion of participants with at least one adverse event (AE) within the first 24 weeks of the study.

**
*Secondary outcomes*
**

1.   The proportion of participants experiencing a T1R or T2R (as separate outcomes) at 24 and 48 weeks.

2.   Time to first LR and time to first T1R and T2R as separate outcomes, over the full 48 weeks.

3.   Severity of T1R and T2R at onset based on investigator-assessed validated Clinical Severity Scores
^
52,
53
^.

4.   The proportion of participants with at least one SAE within the first 24 weeks of the trial.

5.   The total number of AE within the first 24 weeks of the trial.

6.   Cumulative corticosteroid usage in participants with a leprosy reaction.

7.   The proportion of participants experiencing clinical nerve function impairment (NFI) developed over the full 48 weeks.

8.   Quality of Life (QoL) at enrolment, half-way treatment intervention (12 weeks), end of treatment intervention (24 weeks), and end of study (48 weeks) using validated local language versions of the Dermatology Life Quality Index (DLQI) and the 36-item Short Form Survey (SF-36).

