### Randomisation and treatment allocation

**
*Randomisation*
**

All participants who present with newly diagnosed MB leprosy and agree to participate in the trial, will be screened for eligibility. Participants eligible for enrolment, will be randomized to two parallel groups in a 1:1 ratio: metformin for 24 weeks versus identical placebo for 24 weeks. Placebo will be identical in appearance to active drug and contain the inactive ingredients sodium carboxymethyl cellulose, hypromellose and magnesium stearate. It will be dosed and dispensed in the same way as metformin. Randomization will be stratified by BI-score (BI ≥ or < 4) and study site. The randomization list will be computer-generated based on random permuted blocks with variable block size. The randomization list will be generated through a statistical code and securely incorporated within the trial database. Based on the randomization list blinded drug packages (treatment packs are labelled with a different code per site) are distributed to all study sites. A 24h web-based randomization service is provided through
REDCap. Treatment should start as soon as possible after randomization. Unblinding will be performed after the data collection, statistical analysis plan and statistical coding have been completed, or earlier at the individual level, if this is essential for best management of the participant and agreed upon by the Site Principal Investigator (PI) and Chief Investigators. Study medication must be discontinued for an individual after unblinding. All instances of unblinding should be reported to the Data Monitoring Committee (DMC).

**
*Blinding*
**

Identical vials of metformin or placebo tablets will be prepared by the Trial Pharmacist at OUCRU ID’s Clinical Trial Unit. The Trial Pharmacist will make up and label individual-participant blinded treatment packs with trial numbers, containing either active drugs or identical placebo sufficient for 6 periods of 4 weeks of treatment according to the prespecified randomization list. No other study team members including PI, study coordinators and site PI’s, doctors, nurses, laboratory technician’s and pharmacist’s have access to the key of the randomization list.

**
*Treatment discontinuation*
**

The participants may request for any reason to withdraw consent for treatment or the investigator may discontinue treatment for any of the following reasons:

An AE which requires discontinuation of the investigational medicinal product (IMP,

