The primary efficacy outcome is the proportion of participants experiencing a LR during study follow up (total 48 weeks). The effect measure is the treatment difference between the intervention (metformin plus MDT) and control (placebo plus MDT) group. The treatment difference will be quantified in a logistic regression model that includes BI as a continuous variable and study site. Results will be marginalized over BI and study site. We will also consider a model using a log-link, which provides risk ratios. If loss to follow-up is 5% or more, we will take censored data into account and fit the model using pseudo-values. The heterogeneity of the treatment effect will be assessed by including an interaction term between treatment and BI, as well as between treatment and study site (two separate models). For the safety outcome, the proportion of participants with at least one AE within the first 24 weeks will be compared. The chi-squared test will be used to compare the treatment arms, or Fisher’s exact test in case the expected number under the null hypothesis in at least one of the cells is smaller than one. The analyses to be performed will be documented in the Statistical Analysis Plan (SAP), which will be finalized before the database is unlocked and the final analysis with the unblinded data is performed. R software will be used.

**
*Analysis of the secondary outcomes*
**

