For all secondary outcomes, we make a comparison correcting for BI and study site, except for those related to (S)AE (i.e. outcome 4 and 5). Outcomes 1, 4 and 7 are analyzed in the same way as the two primary outcomes. For time to first LR, we compute and plot Kaplan-Meier curves by treatment arm and fit Cox proportional hazards models that include BI and study site. Although the value of the hazard ratio cannot be given a causal interpretation, we include this model because it is the standard approach in time-to-event analyses. However, we will also perform an analysis using restricted mean survival time as outcome. Severity of T1R and T2R at onset will be compared with a regression model that is determined based on the distribution of the scores. The total number of AEs within the intervention period will be compared via a quasi-Poisson regression model. Cumulative corticosteroid usage is modelled via linear regression. For the participants that are still using corticosteroids at 48 weeks, values will be treated as right censored. If needed, we will use the Box-Cox procedure to determine an appropriate transformation. We will allow for extra values at zero via a zero-inflated model, in case some of the participants with a mild reaction do not receive corticosteroids. Quality of life is compared over the four time points using mixed effects models. If the distribution in QoL is too skewed, we will use beta regression using generalized estimating equations to correct for correlation within individuals.

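### The adverse-event comparisons leave out the factors used to stratify randomisation, and the primary safety outcome is planned only as a test, with no estimate of the size of any excess

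*Protocol article*

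**What the plan says.** Under Randomisation, the protocol article states: "Randomization will be stratified by BI-score (BI ≥ or < 4) and study site". Under Design and setting: "The study will take place in five primary health centers (puskesmas) in Jayapura, Papua, and Gowa, Sulawesi". Five sites by two BI levels give up to 10 strata.

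Under Analysis of the primary efficacy and safety endpoints, the efficacy outcome has a named effect measure, a treatment difference from a logistic model with BI and site, marginalised over both. The primary safety outcome, at least one adverse event in the first 24 weeks, is treated differently: "The chi-squared test will be used to compare the treatment arms", with Fisher's exact test when an expected cell count is below one. No effect measure is named for it.

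Under Analysis of the secondary outcomes, the general rule is: "we make a comparison correcting for BI and study site, except for those related to (S)AE (i.e. outcome 4 and 5"). Outcome 4 (any serious adverse event) follows the method of the primary outcomes. Outcome 5 (number of adverse events) gets a quasi-Poisson model without BI or site.

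Quality of life is covered by the BI and site rule. It is measured at four times: "Quality of Life (QoL) at enrolment, half-way treatment intervention (12 weeks), end of treatment intervention (24 weeks), and end of study (48 weeks"). The analysis sentence is: "Quality of life is compared over the four time points using mixed effects models".

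**The concern.** Blocked randomisation within strata balances the arms on BI and site. Differences in risk between strata then largely cancel out of the treatment difference, but an unadjusted standard error still counts them as noise. If event recording varies by site or BI, the test is too cautious. For an efficacy outcome that is a cost to the sponsor. For a safety outcome it makes a real excess slightly harder to see, and Study aims lists tolerability and safety first.

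Site variation is plausible here. Under Safety reporting, non-serious grade 1 or 2 events are recorded only if judged related to the study drug or if they alter MDT. That judgement is made locally, in five centres across two regions.

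The second issue needs no assumption about sites. At about 75 per arm, a non-significant chi-squared test says little on its own about how many extra events remain compatible with the data.

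**Working it through.** **The plan's own figure.** The only power figure is for efficacy: 75 per arm, 50% against 25%, two-sided 0.05. The null SE is √(2 × 0.375 × 0.625/75) = 0.0791, and the alternative SE is √((0.25 + 0.1875)/75) = 0.0764. Then (0.25 − 1.96 × 0.0791)/0.0764 = 1.24, and Φ(1.24) = 0.893. The stated 89% reproduces and is not affected by this point. The article gives no figure for safety or quality of life, so the event risks and correlations below are assumptions.

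**Loss from leaving out site.** Take five equal sites with evenly spaced risks averaging 30%. Total variance is 0.3 × 0.7 = 0.21. Within-site variance is 0.21 minus the between-site variance of the risks.

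- Risks 10, 20, 30, 40, 50%: between-site variance is (0.04 + 0.01 + 0 + 0.01 + 0.04)/5 = 0.02, so within-site variance is 0.19. SE ratio √(0.21/0.19) = 1.051. Size 2 × (1 − Φ(1.96 × 1.051)) = 3.9%.
- Risks 20, 25, 30, 35, 40%: between-site variance is 0.005, so within-site variance is 0.205. SE ratio √(0.21/0.205) = 1.012. Size 4.7%.

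**Check by simulation.** Ten strata of 15, arms nearly balanced within each, 10,000 trials per setting. CMH is the Cochran-Mantel-Haenszel test. Power is for a 20-point excess in every stratum.

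| Stratum risks | Unadjusted SE / true SE | Size, chi-squared | Size, CMH | Power, chi-squared | Power, CMH |
|---|---|---|---|---|---|
| all 30% | 0.99 | 5.1% | 5.2% | 72.1% | 70.4% |
| 20-40% | 1.015 | 4.4% | 4.5% | 71.6% | 71.3% |
| 10-50% | 1.047 | 4.0% | 5.0% | 72.1% | 74.1% |
| 5-75% (extreme) | 1.105 | 3.5% | 5.5% | 69.9% | 78.8% |

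**What a test alone leaves open.** With 75 per arm and an assumed 30% in each arm, the SE of the risk difference is √(2 × 0.21/75) = 0.0748, so the 95% half-width is 14.7 points. An observed difference of zero would still be compatible with an excess of that size. Using the within-site variance of 0.19, the half-width is 1.96 × √(2 × 0.19/75) = 14.0 points. Stating the interval adds more than narrowing it does.

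**Quality of life.** If one arm effect were averaged over all four visits, a constant later difference d would be estimated as (0 + d + d + d)/4 = 0.75d. With arm-by-visit terms there is no dilution. Leaving the enrolment score unused would then inflate a single-visit SE by 1/√(1 − r²), which is 1.048, 1.155 and 1.400 at assumed correlations r of 0.3, 0.5 and 0.7.

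**The case against.** The unadjusted comparison is explicit, simple and valid. It has no bias and no inflated type I error. The article gives no event risks by site and does not say that recording differs between sites. At 20-40% the loss is negligible, and if the strata do not predict events the stratified test has slightly less power (70.4% against 72.1%). Ten strata of about 15 participants with few serious events could make full stratification unstable.

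All of this stands as a limit on size. It does not remove the point. The omission is a stated choice that departs from the treatment of efficacy in the same section. Adjustment also need not use ten cells: BI as a continuous term plus site takes 1 + 4 = 5 coefficients, and a Mantel-Haenszel difference by site copes with few events.

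On quality of life, a reader might infer that the planned model dilutes the effect to three quarters. The text does not support that. It does not say that one arm effect is averaged over the visits, and a model with all four visits and equal arm means at enrolment fits the sentence as written. Correcting for BI and site does not exclude a baseline score. A reader might also infer that the fallback, "we will use beta regression using generalized estimating equations to correct for correlation within individuals", cannot handle scores at the scale limits. That does not follow, because estimating equations need only a mean and a variance function, and these can accommodate such scores.

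**Conclusion.** The point holds as a modest, nearly free improvement to the safety analysis. The primary safety outcome and outcomes 4 and 5 are compared without the randomisation factors. If those factors predict recorded events, the standard error is about 1-2% too large at assumed risks of 20-40% and about 5% too large at 10-50%, with test size about 4.4-4.7% and 4% respectively. There is no loss if they do not predict events, and about 11% in the SE in the extreme setting. A reader might infer that the safety test is invalid or biased. It is neither, only conservative under those assumptions.

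The part that depends on no assumed site pattern is that safety is named only as a test, which does not show how large an excess is ruled out. The quality-of-life wording is under-specified, not wrong, and supports a suggestion only.

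**What to change.** - **Primary safety outcome:** report a BI- and site-adjusted risk difference with 95% confidence interval, from the marginalised model already planned for efficacy, or Mantel-Haenszel by site when events are few.
- **Outcome 4:** treat in the same way.
- **Outcome 5:** add BI and site to the quasi-Poisson model.
- **Suggestion for quality of life:** use the enrolment score as covariate, or keep all four visits with arm means constrained equal at enrolment, and report the post-baseline differences. The constrained form also keeps participants with a missing enrolment score.

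The cost is a change of wording and a few lines of code. BI, site and enrolment quality of life are already collected. The article reports enrolment as ongoing and says the SAP is finalised before the unblinded final analysis, so as of this version there is room for the change. The downside is that sparse serious-event counts may allow fewer adjustment terms, so the SAP should set the fallback in advance.

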### Ethical considerations

**
*Consent*
**

Before any of the trial-related procedures are conducted, the participant or a legally acceptable surrogate (if the participant lacks capacity) must undergo an informed consent procedure in their own language. Participants will be informed about the exact nature of the study, potential side-effects of metformin and MDT, signs and symptoms of LR and NFI and any risks involved in taking part. Participants will be advised to immediately return to the clinic once symptomatic complaints or abnormalities occur. Participants and/or surrogates will be given proficient time to consider participation in the trial and ask questions if needed. The PI is responsible for ensuring that all vulnerable participants are protected and participate voluntarily in an environment free from coercion or undue influence. If consent was provided by a relative, the participant should be consulted and consent recorded if and when they have the capacity to do so. A separate, optional, storage consent will be asked for long term storage of blood and skin samples for future immunogenetic research. Absence of this consent, does not effect trial eligibility.

**
*Confidentiality*
**

The trial will be conducted in accordance with the principles of the Declaration of Helsinki. All participant-related information will be kept confidential. Participants will be identified by a unique study identification number that will be used for documentation (i.e. case report forms, IMP labels, samples) and stored in secure locked locations at each site. Electronic data will be stored in password-protected databases of which only study staff have access to. Scientific publications, reports or presentations will never identify participants by name or initials. When the research team reviews clinical notes, they are bound by professional confidentiality. Clinical information will not be released without written permission, except as necessary for monitoring, audit and inspection purposes. Study documentation will be kept in a secure location and held for 15 years after the end of the trial.

**
*Withdrawal*
**

Each participant has the right to withdraw from the study at any time. If a participant withdraws from the trial, the medical data collected during their previous consented participation in the trial will be kept and used in the analysis. Participants who stop the trial within 24 hours of enrolment will be replaced. Participants who stop the trial follow-up hereafter will not be replaced, as the total sample size includes adjustments for loss to follow-up.

**
*Ethical approval*
**

Ethical approval has been obtained from Universitas Gadjah Mada Research Ethics Committee (KE/FK/0695/EC/2021; 21.06.2021), Observational/Interventions Research Ethics Committee of the London School of Hygiene & Tropical Medicine (26618; 02.03.2022) and Oxford Tropical Research Ethics Committee (14-21; 29.07.2021). Approval has been received from the Indonesian drug regulatory authority (RG.01.06.1.3.04.22.76; 28.04.2022). Additional permissions have been received from the clinical sites and local governments. Future amendments to the study protocol will be approved by above parties before being implemented.

### Data sharing and dissemination

The study is registered at ClinicalTrials.gov (NCT05243654; 17.02.2022) and at Indonesian research registry (NA-ZBMDZ7C; 02.06.2022). OUCRU ID has a data sharing policy in place. Data exchange complies with local Information Governance and Data Security policies. Study results will be shared through presentations at scientific conferences and peer-reviewed journals. The collected data will help build evidence-based guidelines and provide opportunities for dissemination and engagement with local communities, stakeholders and (inter)national policy makers. The sites and collaborators participating in this study have an excellent position to disseminate results and influence practice and policy in and outside of Indonesia. Trial results will be reported in concordance with the CONSORT checklist.

### Trial committees

The trial sponsor is the University of Oxford. The TMG will be formed to oversee the management and progress of the trial. This will include the chief investigator, site PIs, study coordinator, co-investigators, trial statistician, and/or data manager. The group will meet quarterly or more often as required. The DMC will advise the TMG regarding continuation, modification or premature closure of the trial.

### Trial status

The trial is currently enrolling participants. The sites in Jayapura, Papua, started enrolling participants in October 2022 and the sites in South Sulawesi in April 2023.

## Discussion

LR are the most important cause of irreversible nerve damage in persons affected by leprosy, even though the immunopathogenesis is poorly understood. LR are a major clinical challenge as they are often chronic, recurrent and require long-term use of systemic corticosteroids causing (S)AE. Adjunct HDT may have the potential to improve immunological responses and thereby reduce nerve pathology, disability and corticosteroid-associated morbidities. The TRIPOD I trial illustrated that low-dose prophylactic corticosteroids prevented LR and NFI in MB leprosy in the short-term, but had no effect after one year
^
73
^. Repurposing immunomodulating drugs, such as metformin, as adjunct HDT may offer a potentially attractive approach that has a biological basis, is safe, affordable, widely available and, if effective, could be relatively easily implemented. The MetLep Trial will be the first double-blind randomized clinical trial evaluating the efficacy, tolerability and safety of adjunctive metformin combined with MDT in persons with MB leprosy to mitigate LR and subsequent nerve damage and corticosteroid use and to further elucidate its immunopathogenesis. If Phase 2 trial results are positive, this trial will inform the design of a Phase 3 efficacy trial with extended follow-up.

## Data Availability

No data are associated with this article. Oxford University Research Archive: SPIRIT checklist for ‘Metformin as adjunctive therapy in combination with multidrug treatment for multibacillary leprosy: A protocol for a randomized double-blind, controlled Phase 2 trial in Indonesia (MetLep Trial)’.
https://doi.org/10.5287/ora-jbn07qyzd
^
51
^. Data are available under the terms of the
Creative Commons Attribution 4.0 International license (CC-BY 4.0).
